### Safety Assessment

Safety evaluation indicators include physical examination, vital signs (heart rate, respiration, body temperature, and blood pressure), laboratory examinations, and AEs. Laboratory examinations will include routine blood tests, routine urinalysis, blood biochemistry, coagulation, blood lipids, fasting blood glucose, HbA1c, and 12-lead electrocardiogram. Specifically, blood biochemistry will include alanine aminotransferase (ALT), aspartate aminotransferase (AST), alkaline phosphatase (AKP), total bilirubin (TBIL), γ-glutamyl transferase (GGT), creatinine (Cr), blood urea nitrogen (BUN). Coagulation indices include prothrombin time (PT), activated partial thromboplastin time (APTT), thrombin time (TT), fibrinogen (FIB). Blood lipids examinations will include TC, TG, HDL-C, and LDL-C.

During the treatment period, investigators should pay attention to observe the AEs and unanticipated toxic side effects (including symptoms, signs, and laboratory tests). Regardless of whether the AE is related to the trial drug, it must be recorded in case report form (CRF) in detail, including the occurrence time, symptoms, signs, degree, duration, laboratory test indicators, treatment methods and results, elapsed time, and follow-up time. If instances of an angina attack, subjects should take one nitroglycerin tablet under the tongue at a time, and can repeat one tablet every 5 min until the pain is relieved. If the pain persists after the total amount reaches three tablets within 15 min, medical attention will be immediately requested.

### System Biological Index

Twenty subjects per group will be randomly selected for metabolomics, proteomics, and transcriptome examinations to explore the biomarkers of TJC in treating T2DM-CHD.

Blood collection requirements will consist of fasting for 10 h before sampling at study start (0 weeks) and after treatment (12 weeks), a single blood collection 5 ml, samples will be centrifuged, and serum stored in an EP tube at −70°C; Urine collection requirements will consist of fasting for 10 h before taking medicine (water is permitted), and fasting (both food and water) for 2 h before urine sampling (−1 h) to 2 h after taking the medicine, drinking water quantitatively for 2–8 h after taking the medicine, and eating low-fat meals 4 h after taking the medicine. Urine will be collected and transferred to EP tubes before taking the medicine (0 h) and after treatment (12 weeks), and kept frozen at −70°C.

### Sample Size Calculation

In this study, the sample size is determined by the proportion of subjects whose CCS classification decreased ≥1 after 12 weeks of medication. According to the results of our clinical trials (unpublished data) and our clinical experience, after a 12 weeks intervention, we assume the proportion of subjects whose CCS classification will decrease by ≥ 1 will be 85% in the treatment group and 70% in the placebo control group. Given a type I error rate of *α* = 0.025, a power of 80% (type II error rate of *β* = 0.2), and considering of 20% possible dropout rate, 236 patients should be allocated to the treatment group and 118 patients in the placebo group. For the convenience of randomization, the final sample size was set at 240 cases in the treatment group and 120 cases in the placebo group.

### Randomization

Subjects who sign the informed consent will be randomly assigned a unique screening number through the central randomization system for screening-related examinations and assessments. Eligible subjects will be enrolled according to the time sequence and drug number. The statistical analysis uses the PROC-PLAN process of SAS software to generate computerized random assignment tables. Drugs used in the trial will be coded according to a random allocation table and then randomly assigned to subjects. Note that patients who failed to screen but are suitable for re-screening must use the original screening number; the drug number of the patients who have been screened successfully but have not received the treatment cannot be reassigned to others. The next successfully screened patient will be assigned the next drug number in sequence.

### Data Collection and Management

The investigator will input the original data into the CRF accurately in strict accordance with the trial protocol and in a timely fashion based on the original observations of participants. To ensure the accuracy of the data, two personnel specializing in data entry should undertake double-entry and proofreading independently. The auditor shall monitor whether all CRFs have been completed and are consistent with the original data, and issue questions at any time in case of any problems. If errors and omissions are made, the researcher shall be corrected promptly.

### Monitoring

To further ensure the quality of clinical trials, the basic principles of "quality by design" and in-process control will be followed (Qu et al., 2019). Before the start of the study, the sponsor will conduct training for the researchers and physicians involved in all centers to ensure the uniformity of administration of medications. The sponsor entrusts the inspector to carry out systematic inspection on the clinical trial and to inspect the trial according to the Good Clinical Practice (GCP) principles to ensure that the test scheme is carried out following the provisions and that the data recorded in the case record form are the same as the original data.

### Statistical Analysis

The statistical analysis plan will be specified before the final data analyses. The statistical analyses will be undertaken via Statistical Analysis System 9.4 (SAS Institute, Inc. Cary, NC) by the Department of Medical Statistics, at the National Center for Cardiovascular Diseases, Beijing. Data from all patients who undergo randomization will analyzed according to the intention-to-treat (ITT) principle. Consistent with the CONSORT statement and ITT principle, the last observation carried forward method will be used for missing values.

For quantitative data, we will calculate the mean, standard deviation, median, minimum, maximum, and interquartile range. For qualitative data, we will describe various frequencies or percentages. The student’s t-test will be used for quantitative data with normal distribution, while the Wilcoxon rank sum test will be used for quantitative data without normal distribution. The chi-square test or Fisher’s exact test will be used for qualitative data. We will analyze intra-group or inter-group differences before and after treatment. Concerning primary outcome, the effectiveness rate of patients whose CCS classification decreased ≥1 after 12 weeks of medication, the differences intra-group or inter-group will be compared using the CMH chi-square test adjusted for clinical site. We will include sex, center, baseline CCS classification, baseline HbA1c level, and baseline lipid levels as covariates in an analysis of covariance (ANCOVA) for statistical differences between groups by reducing the error variance. Statistical Significance will be assumed at a two-sided p-value less than 5%. The relative risk with corresponding 95% confidence interval (CI) to compare dichotomous variables will be calculated.

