#### Withdrawal Criteria

 ◆Signs of exacerbation or deterioration clearly related to the intake of the study drug;◆Comorbidities, complications, adverse events (AEs), or serious AEs (SAEs) occurring during the study;◆Concomitant use of forbidden drugs or receipt of prohibited treatment potentially influencing efficacy and safety;◆Subjects who request to withdraw from the study;◆Poor compliance by subjects or the amount of drug used does not meet the regulations (less than 80% or more than 120%);◆Subjects who have reached the clinical recovery standard before the full course of treatment, and have applied for termination of medication.◆Blinding is uncovered or emergency unblinding is required.

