### Study Procedure

A time schedule of the study procedures is presented in Table 1. The study will include screening/baseline period and treatment period. The duration of the screening/baseline period will be 2 weeks, while the treatment period will be 3 months. Patients will be requested to provide informed consent in writing before the screening period following a full explanation of the study.

**TABLE 1 T1:** Study schedule.

Research phase	Screening/baseline	Treatment phase		
Number of visits	Visit 1	Visit 2	Visit 3	Visit 4
Visit time point	D-14–0	Week 4 ± 4 days	Week 8 ± 4 days	Week 12 ± 4 days
Data collection				
Written informed consent	●			
Inclusion/exclusion criteria	●			
Demographics	●			
Obtain central random number	●			
Previous history, medical history, and allergies	●			
Comorbidities and co-medications	●			
Access to internet hospital "[name]" platform	●			
Safety evaluation				
Vital signs and physical examination	●	●	●	●
Blood routine	●			●
Urine routine	●			●
Blood biochemistry testing (AST, AKP, TBIL, GGT, Cr, BUN)	●			●
Coagulation testing (PT, APTT, TT, FIB)	●			●
12-Lead ECG	●			●
Urine pregnancy test	●			●
Efficiency evaluation				
CCS Classification	●	●	●	●
Treadmill exercise test	●			●
Fasting blood glucose	●			●
Glycosylated hemoglobin	●			●
Weekly nitroglycerin dosage	●	●	●	●
Blood lipid examination (TC, TG, HDL-C, LDL-C)	●			●
Seattle angina questionnaire scores	●	●	●	●
Other jobs				
Distribute experimental drugs	●	●	●	
Recall test drug		●	●	●
Record AEs and combined medications		●	●	●
Compliance judgment		●	●	●

Abbreviations: ECG, electrocardiogram; CCS, Canadian Cardiovascular Society; ALT, alanine aminotransferase; AST, aspartate aminotransferase, AKP, alkaline phosphatase; TBIL, total bilirubin; GGT, *γγ*-glutamyl transferase; Cr, creatinine; BUN, blood urea nitrogen; PT, prothrombin time; APTT, activated partial thromboplastin time; TT, thrombin time; FIB, fibrinogen; TC, total cholesterol; TG, triglyceride; HDL-C, high-density lipoprotein cholesterol; LDL-C, low-density lipoprotein-cholesterol; AE, adverse event.

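### The last-observation-carried-forward rule is not limited to efficacy, so for laboratory tests and ECG scheduled only at baseline and Week 12 it can enter the pre-treatment value as the Week 12 result

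*Protocol article*

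**What the plan says.** The Statistical Analysis section fixes the population: "Data from all patients who undergo randomization will analyzed according to the intention-to-treat (ITT) principle". It then fixes the handling of incomplete data: "Consistent with the CONSORT statement and ITT principle, the last observation carried forward method will be used for missing values". The sentences that follow give general methods for quantitative and qualitative data, and the primary outcome is singled out only after that. No separate rule or population for safety data is stated.

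Safety Assessment defines the laboratory part of safety: "Laboratory examinations will include routine blood tests, routine urinalysis, blood biochemistry, coagulation, blood lipids, fasting blood glucose, HbA1c, and 12-lead electrocardiogram". Fasting glucose, HbA1c and the lipids also appear under Secondary Outcomes.

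The study schedule (Table 1) marks these tests at two visits only, Visit 1 (screening/baseline) and Visit 4 (Week 12). The coagulation row, "Coagulation testing (PT, APTT, TT, FIB", is an example. Vital signs and physical examination are marked at all four visits.

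Withdrawal Criteria include "Comorbidities, complications, adverse events (AEs), or serious AEs (SAEs) occurring during the study". Safety Assessment requires each adverse event to be entered in the CRF with, among other items, "laboratory test indicators, treatment methods and results, elapsed time, and follow-up time".

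**The concern.** LOCF needs an on-treatment observation to carry. For measures taken once before treatment and once at Week 12, a patient who leaves in between has no scheduled on-treatment value. A literal application enters the pre-treatment result as the Week 12 result. That imputed zero is then counted as a real observation in means, standard deviations and shift counts.

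Two things are at stake. The laboratory and ECG summaries would look more precise than the data allow. And because patients may be withdrawn for adverse events, the patients who receive imputed zeros may not be a random subset. This differs from LOCF for the CCS response, which is assessed at Weeks 4 and 8 as well, so an on-treatment value will often exist.

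**Working it through.** **Inputs from the plan.** The point borrows only the 20% dropout and the arm sizes of 240 and 120 from Sample Size Calculation, and disputes neither. As a check on that section: 85% against 70%, 2:1 allocation, alpha 0.025 read as one-sided, 80% power and unpooled variance give a placebo size of

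(0.70 × 0.30 + 0.85 × 0.15 / 2) × (1.9600 + 0.8416)² / 0.15² = 0.27375 × 7.849 / 0.0225 = 95.5,

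and 95.5 / 0.8 = 119.4, so 120. This is within two of the stated 118, which was then set to 120.

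**Which measures are exposed.**

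| Measures | Scheduled | Role in the plan |
|---|---|---|
| Blood and urine routine, biochemistry, coagulation, ECG | Visit 1 and Week 12 | Safety |
| Fasting glucose, HbA1c, TC, TG, HDL-C, LDL-C | Visit 1 and Week 12 | Secondary outcome and safety |
| Vital signs, physical examination | All four visits | Safety; outside this point |

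**How many patients.** 0.20 × 240 = 48 and 0.20 × 120 = 24. These are upper bounds, since some who stop early may still have a later test. At 10% dropout they are 24 and 12; at 5%, 12 and 6.

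**Dropout unrelated to the result.** Let d be the share with an imputed zero, m and σ the mean and SD of the change among those observed, and n the arm size.

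- Mean under LOCF: (1 − d)m = 0.8m at d = 0.20.
- Variance under LOCF: (1 − d)σ² + d(1 − d)m², about (1 − d)σ² when m is small relative to σ.
- SE under LOCF: σ√(1 − d)/√n. SE from observed data: σ/√((1 − d)n). Their ratio is 1 − d = 0.8.
- Mean divided by SE: 0.8 / 0.8 = 1, so the test ratio is roughly unchanged.

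**Unequal dropout.** The between-arm difference under LOCF is (1 − d_T)m_T − (1 − d_P)m_P. Suppose both arms truly change by m, with assumed dropout of 20% on TJC and 10% on placebo. The difference becomes 0.8m − 0.9m = −0.1m, although the truth is zero. If m is a deterioration, TJC looks better; if m is an improvement, TJC looks worse.

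**Dropout related to harm (assumed rates, not in the documents).** Take 2% abnormal at Week 12 among completers, normal baselines in those who leave, and 2%, 25% or 50% truly abnormal among them. LOCF shows (1 − d) × 2%. The true rate is (1 − d) × 2% + d × (2%, 25% or 50%).

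| Dropout | LOCF | Completers only | True: 2% / 25% / 50% among leavers |
|---|---|---|---|
| 5% | 1.9% | 2.0% | 2.0% / 3.2% / 4.4% |
| 10% | 1.8% | 2.0% | 2.0% / 4.3% / 6.8% |
| 20% | 1.6% | 2.0% | 2.0% / 6.6% / 11.6% |

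In the 20% and 25% cell, the gap due to LOCF itself is 2.0 − 1.6 = 0.4 percentage points. The remaining 6.6 − 2.0 = 4.6 points arise because those patients have no Week 12 test. Dropping the imputation does not recover them; only unscheduled on-treatment values can.

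**The case against.** The strongest reply is that the article never says LOCF covers safety tests. The sentence is justified by ITT, the section announces that "The statistical analysis plan will be specified before the final data analyses", and a condensed article commonly leaves safety populations and shift tables to that plan. This stands in part: that the rule reaches purely safety variables is a literal reading, not an explicit statement, and the later plan may narrow it. It does not dispose of the point, because the article states a rule rather than staying silent, and the later plan would have to override it. Even on an efficacy-only reading, LOCF reaches fasting glucose, HbA1c and the four lipids, which are listed in both roles.

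A reader might go further and infer several things that the documents do not support:

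- *That harm is analysed as no change.* Each adverse event is recorded whether or not it is related to the drug, and LOCF does not alter those counts. Only the Week 12 laboratory and ECG summaries are diluted.
- *That baseline is certain to be carried.* An unscheduled value taken when toxicity was found could be the last observation. The rule does not say whether such values count.
- *That the error always favours a clean safety result.* The unequal-dropout case shows either direction is possible. A patient abnormal at baseline who later normalises would also stay abnormal under LOCF.
- *That the test is pulled towards no effect, or that a reported upper limit for harm is too low.* Under non-informative dropout the test ratio barely moves, and the section plans confidence intervals only for relative risks of dichotomous variables.
- *That the article attributes platelet inhibition to TJC.* The Introduction says this of two component herbs.

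**Conclusion.** The point holds in this limited form. Applied as written, the rule enters the pre-treatment value at Week 12 for early leavers on every laboratory and ECG measure scheduled at only two visits, unless an unscheduled value is counted as the last observation. At 20% dropout, up to 48 and 24 patients are affected, and each arm's mean change and SE fall to about 0.8 of the observed-data values. The 0.8 assumes non-informative dropout, a mean change that is small relative to its SD, and every leaver lacking a Week 12 test. Where dropout is related to harm, the documents give no rates, so neither the size nor the between-arm direction can be fixed. It is worth correcting because the rule is stated and the remedy is cheap. It is not evidence that adverse events would be hidden.

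**What to change.** In Statistical Analysis, and in the analysis plan that follows:

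1. Limit LOCF, or whatever replaces it, to efficacy outcomes.
2. State that safety data are analysed as observed, without imputation, in patients who took at least one dose.
3. For each laboratory and ECG variable, tabulate by arm the shift from baseline to the worst recorded post-baseline value, including unscheduled values recorded with an adverse event or at withdrawal.
4. Show by arm how many patients have no post-baseline value.
5. Apply the same rule to the safety tables for fasting glucose, HbA1c and lipids; their efficacy analyses may follow the efficacy rule.

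The cost is one or two sentences and a set of shift tables built from data the CRF is already meant to hold. No visit, dose or withdrawal rule changes. The downside is smaller safety denominators and wider intervals: at 20% dropout, 1 / 0.8 = 1.25 times the LOCF width for a mean change, which is the width the data support.

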#### Secondary Outcomes

The secondary outcomes of the study medication will be determined by: ◆Treadmill exercise test (conducted partially by subjects). The evaluation indexes include total treadmill exercise time, the appearance of ST-segment 1 mm depression time, the duration of exercise-limited angina, Duke treadmill score (Salokari et al., 2019), rate-pressure product, metabolic equivalents. The amounts of ST-segment deviations is defined as the maximal deviated values (mm) of ST segments on any lead.◆Fasting blood glucose and glycosylated hemoglobin (HbA1c);◆Weekly nitroglycerin dosage;◆Blood lipid examinations including total cholesterol (TC); triglyceride (TG); high-density lipoprotein cholesterol (HDL-C); low-density lipoprotein-cholesterol (LDL-C);◆Seattle angina questionnaire (SAQ) scores (Chan et al., 2014);

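### Continuous secondary outcomes are assigned unadjusted tests, and the ANCOVA covariate list omits the own baseline of 9 of 14 measures although all are collected, so precision is lost

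*Protocol article*

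**What the plan says.** All of the following is in the protocol article.

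- **Test for continuous data (Statistical Analysis).** The rule is that the "t-test will be used for quantitative data with normal distribution, while the Wilcoxon rank sum test will be used" otherwise. Neither test carries a baseline adjustment.
- **What is compared (Statistical Analysis).** "We will analyze intra-group or inter-group differences before and after treatment". This does not settle whether the between-group test uses the change from baseline or the Week-12 value.
- **ANCOVA (Statistical Analysis).** The covariates are "sex, center, baseline CCS classification, baseline HbA1c level, and baseline lipid levels as covariates", and the stated aim is to test "for statistical differences between groups by reducing the error variance". The sentence comes after the one on the primary outcome and does not name the outcomes to which it applies.
- **Secondary outcomes (Secondary Outcomes).** The treadmill test contributes six indices, among them "total treadmill exercise time, the appearance of ST-segment 1 mm depression time, the duration of exercise-limited angina"; only some participants perform it. The others are fasting glucose, HbA1c, weekly nitroglycerin dosage, four lipids and SAQ scores.
- **Timing (Table 1).** Every one of these is scheduled at Visit 1 and Week 12. Nitroglycerin and SAQ are also recorded at Weeks 4 and 8.

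**The concern.** For a continuous measure taken before and after treatment, the same measure at baseline is usually the best single predictor of the final value. The protocol says it wants to reduce error variance, yet its list would adjust treadmill time for lipids and HbA1c but not for baseline treadmill time.

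The treadmill results matter most here. The Study Objectives frame the trial around exercise tolerance as well as heart function, while the primary outcome is angina class. The treadmill indices are therefore the direct evidence on exercise tolerance, and they come from a smaller sample in which precision is scarcer. What is at stake is wider confidence intervals and lower power for those secondary comparisons than the collected data would allow.

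**Working it through.** **1. The plan's own figure.** The protocol gives no power, variance or correlation for any secondary outcome. Its one calculation is for the binary primary outcome: 70% against 85%, 2:1 allocation, α = 0.025, power 80%, 20% dropout. Reading α as one-sided, with unpooled variance:

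(0.70 × 0.30 + 0.85 × 0.15 / 2) × (1.960 + 0.842)² / 0.15² = 95.5 controls; 95.5 / 0.8 = 119.4, about 120.

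The stated figure is 118, so it is reproduced to within two patients. Nothing below changes it.

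**2. Which measures have their own baseline in the list.**

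| Measure | Number | Own baseline listed? |
|---|---|---|
| Treadmill indices | 6 | No |
| Fasting glucose | 1 | No |
| Weekly nitroglycerin dosage | 1 | No |
| SAQ (counted as one score) | 1 | No |
| HbA1c | 1 | Yes |
| TC, TG, HDL-C, LDL-C | 4 | Yes |

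Total 14: listed 1 + 4 = 5; not listed 6 + 1 + 1 + 1 = 9.

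**3. Relative variance of the treatment effect.** Let r be the correlation between baseline and Week 12, with equal variances at the two times. Relative variances are:

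- test of Week-12 values: 1
- test of change scores: 2(1 − r)
- ANCOVA on own baseline: 1 − r²

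The ratio of ANCOVA to the Week-12 test is 1 − r². The ratio of ANCOVA to the change-score test is (1 − r²) / [2(1 − r)] = (1 + r)/2. Neither exceeds 1 for r from 0 to 1, so the direction does not depend on the value of r.

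**4. Size.** The correlation is an assumption: 0.5 to 0.7 as the working range, 0.3 and 0.8 as outer limits. Power is that of ANCOVA for an effect that the comparator test would detect with 80% power: Φ[(1.960 + 0.842)/√ratio − 1.960].

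| r | Ratio to Week-12 test | Reduction | Power | Ratio to change test | Reduction | Power |
|---|---|---|---|---|---|---|
| 0.3 | 0.91 | 9% | 84% | 0.65 | 35% | 93% |
| 0.5 | 0.75 | 25% | 90% | 0.75 | 25% | 90% |
| 0.6 | 0.64 | 36% | 94% | 0.80 | 20% | 88% |
| 0.7 | 0.51 | 49% | 97.5% | 0.85 | 15% | 86% |
| 0.8 | 0.36 | 64% | 99.7% | 0.90 | 10% | 84% |

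Against change scores at r = 0.5 to 0.7, the gain is worth 1/0.85 = 1.18 to 1/0.75 = 1.33, that is 18–33% more patients.

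**5. Both readings of the ANCOVA's scope.** If it covers the secondary outcomes, nine lack their own baseline. If it does not, all 14 have only the unadjusted tests. The comparators in step 4 are unadjusted tests, so the figures apply fully to the second reading. On the first, the further reduction from adding the own baseline is the squared partial correlation given the covariates already listed, which the documents do not allow one to compute.

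**The case against.** The strongest reply is that a condensed article leaves outcome-by-outcome models to the analysis plan, which the protocol says will be specified before the final analysis. The text says which covariates will be included, but it neither closes the list nor ties it to particular outcomes. This stands in part: a reader might infer that a wrong model has been fixed for every secondary outcome, and the text does not go that far. But the protocol does name the tests and the covariates, and a plan that simply followed it would carry the omission forward.

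Three other inferences go too far:

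- **That chance baseline imbalance goes uncorrected.** If the before-and-after sentence means change scores, each outcome's own baseline is already used, though less efficiently. The 25–49% figure then does not apply; 15–25% does.
- **That the full gain applies everywhere.** If the ANCOVA does cover these outcomes, listed covariates may already capture some of it, for example baseline HbA1c for fasting glucose or baseline CCS class for SAQ. The correlation also need not be the same for all nine measures.
- **That choosing between t and Wilcoxon by normality damages the error rate.** The protocol states the conventional rule without saying how normality is judged, and no error-rate consequence has been shown.

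Unadjusted tests in a randomised trial are valid. The point concerns efficiency only.

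**Conclusion.** The point holds as a loss of precision in continuous secondary outcomes. Nine of 14 measures lack their own baseline in the covariates named, although Table 1 collects it. There is no bias and no effect on the binary primary outcome, for which baseline CCS class is in any case among the covariates.

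With an assumed correlation of 0.5 to 0.7 and equal variances, the avoidable variance is 15–25% if change scores are tested and 25–49% if Week-12 values are tested. It is less where the listed covariates already predict the outcome. The direction is secure on either reading. The size is not, because the protocol gives no correlation and does not state the ANCOVA's scope or the quantity compared. For the treadmill indices, the gain applies to the subset tested.

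**What to change.** In the analysis plan:

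1. State that the ANCOVA covers the continuous secondary outcomes.
2. Add each outcome's own baseline to the covariates already listed, leaving those in place.
3. Make this model, with the Week-12 value as the response, the main between-group analysis of each such outcome. Use a rank or transformed scale for skewed measures such as nitroglycerin dosage.
4. Keep the t and Wilcoxon tests as sensitivity analyses.

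The cost is wording, plus one extra model term for each of the nine outcomes. No additional data, visits or patients are needed.

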### Study Design

This study was designed as a randomized, double-blinded, parallel controlled, multicenter clinical trial. A total of 360 eligible participants will be randomly divided into treatment group and control group in a ratio of 2:1. This study was prospectively registered with Chinese Clinical Trial Registry (ChiCTR2000037491) in September 2020. The study flow is shown in Figure 1.

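### Student's t-test is planned for normally distributed outcomes with no provision for unequal variances, although allocation is 2:1; the Welch form is a nearly free improvement for secondary and safety outcomes

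*Protocol article*

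**What the plan says.** The Statistical Analysis section of the protocol article sets one rule for quantitative data. The Student "t-test will be used for quantitative data with normal distribution, while the Wilcoxon rank sum test will be used" when the data are not normal. Normality is the only condition that moves an outcome from one test to the other. Equal or unequal variances are not mentioned, and neither is the unequal-variance form of the t-test. The level is set by "Statistical Significance will be assumed at a two-sided p-value less than 5" per cent. The same section plans an ANCOVA for differences between the groups. It states a 95% interval only for the relative risk of dichotomous variables. It also says that a statistical analysis plan will be specified before the final analyses.

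Under Study Design, patients are "randomly divided into treatment group and control group in a ratio of 2:1". Under Sample Size Calculation, "the final sample size was set at 240 cases in the treatment group and 120 cases in the placebo group".

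The primary outcome is the proportion of patients whose CCS class falls by at least one. It is tested by a CMH chi-square test, not a t-test. The t-test rule therefore applies to the quantitative secondary outcomes (treadmill indices, glucose, HbA1c, lipids, SAQ scores and nitroglycerin use) and to the quantitative safety measures, where these are judged normal.

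**The concern.** With equal arms, pooling the variance is close to harmless even if the SDs differ. With 2:1 arms it is not. About two thirds of the weight in the pooled variance comes from the TJC arm, whereas the true variance of the difference in means depends more on the placebo arm, because that arm is half the size. If placebo is the more variable arm, the pooled standard error is too small and the test rejects too often. If TJC is the more variable arm, it is too large and power is lost. A check for normality does not detect this, because two normal samples can have different SDs. A larger sample does not cure it, because the distortion depends on the ratio of the arm sizes.

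At stake is whether tests of the normally distributed secondary and safety measures keep their stated 5% level and their power. The treadmill indices deserve particular care, because the Study Objectives section states the hypothesis partly in terms of exercise tolerance.

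**Working it through.** **Inputs from the article.** Arms of 240 and 120; dropout 20% ("considering of 20% possible dropout rate"), which leaves 192 and 96; two-sided level 5%.

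**Assumption.** No SD is given for any continuous outcome. The ratio r = SD(placebo)/SD(TJC) is therefore assumed and varied, with SD(TJC) set to 1.

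**The plan's own figure.** The article gives no figure for the t-test, but its arm sizes can be checked. With 85% v 70%, 2:1 allocation, 80% power and 0.025 read as one-sided (equal to 0.05 two-sided), the unpooled formula gives for placebo

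(1.96 + 0.8416)² × (0.70×0.30 + 0.85×0.15/2) / 0.15² = 7.849 × 0.27375 / 0.0225 = 95.5, so 96.

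Dividing by 0.8 for dropout gives 120, and 240 for TJC. The article has "236 patients should be allocated to the treatment group and 118 patients in the placebo group" before rounding up to 120 and 240, so the arm sizes reproduce closely. They rest on the binary outcome and do not depend on the t-test.

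**Step 1: standard errors.**
- Pooled variance: s² = [(240−1) + (120−1)r²] / 358
- Squared standard error used by Student's t: s² × (1/240 + 1/120) = s² × 0.0125
- Correct squared standard error: 1/240 + r²/120
- k = square root of (used / correct)

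Example with r = 1.25: s² = (239 + 119×1.5625)/358 = 1.187. Used: 0.01484. Correct: 0.004167 + 0.013021 = 0.01719. So k = √(0.01484/0.01719) = 0.929.

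**Step 2: true error when the means are equal.** Error = 2Φ(−1.96k).

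| r (placebo:TJC) | k | True two-sided error |
|---|---|---|
| 0.8 | 1.076 | 3.5% |
| 0.9 | 1.036 | 4.2% |
| 1.0 | 1.000 | 5.0% |
| 1.1 | 0.969 | 5.8% |
| 1.25 | 0.929 | 6.9% |
| 1.5 | 0.879 | 8.5% |

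Simulation of normal data at 240/120 (200,000 trials per ratio) gave 3.5%, 4.3%, 5.0%, 5.8%, 6.9% and 8.5% for the same rows. Results at 192/96 were the same within simulation error. Welch's test stayed at 4.9% to 5.1% throughout.

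**Step 3: power lost when TJC is the more variable arm (r = 0.8).** Take a true difference for which the correct standard error gives 80% power, that is 1.96 + 0.8416 = 2.8016 standard errors. With the pooled standard error, power is Φ(2.8016 − 1.96×1.076) = Φ(0.692) = 75.6%, a loss of about 4 points.

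**Step 4: price of Welch when the SDs are equal.** By simulation, 80.1% for Student's t v 80.0% for Welch at 240/120, and 80.0% v 79.9% at 192/96. The cost is about 0.1 point.

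**The case against.** Four objections have force.

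*No effect means no problem.* If TJC does nothing at all, randomisation gives both arms the same outcome distribution and so the same SD. Student's t then holds its level: a simulated bounded score with no effect (assumed mean 85, SD 20, limits 0 and 100, 240/120) was rejected 4.9% of the time. This stands. The error rates above apply only where TJC changes the spread but not the mean. A change in both leaves the standard error wrong, but a significant result is then not a false positive.

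*Ceiling and floor outcomes.* A reader might infer that SAQ scores near their maximum and nitroglycerin use near zero would make the TJC arm less variable, and so make results look too significant. The article does not support this. Such data are clearly non-normal and the plan sends them to the Wilcoxon test. In assumed ceiling and low-count scenarios at 192/96, with Shapiro-Wilk applied per arm (the article names no normality test), both arms never passed in 3,000 runs each.

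*Intervals.* A reader might also infer that the planned confidence intervals are wrong. The only interval that the article plans is for the relative risk. The point would reach intervals only if mean differences were also reported with pooled ones.

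*Detail for the analysis plan.* The article is condensed, uses a generic test name and defers to a plan not shown, so the pooled form is not stated outright. That lowers the weight of the point. It does not remove it: the article names a specific test and a single rule for leaving it, and a plan written to that wording would ordinarily inherit the pooled form.

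**Conclusion.** The point holds as a free improvement to the plan, not as a demonstrated error. Read in its standard form, Student's t-test has a pooled standard error that is wrong at 2:1 whenever TJC alters the spread of a normally distributed outcome, and the stated rule has no safeguard against that. For assumed SD ratios of 0.8 to 1.5 with equal means, the true error runs from about 3.5% to 8.5%. For mild differences (0.9 to 1.1) it is about 4.2% to 5.8%, which matters little.

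The documents contain no SDs, so neither the size nor the direction of any distortion is known. It would go too far to say that significance will be overstated, since the test is conservative if TJC is the more variable arm. Only normally distributed secondary and safety outcomes are concerned. The primary CMH test, the sample size and its power are not affected.

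**What to change.** In the analysis plan, before unblinding, state that between-arm comparisons of means use the unequal-variance (Welch/Satterthwaite) t-test. Where ANCOVA is used for a continuous outcome, state that it uses robust standard errors or arm-specific residual variances. An ordinary ANCOVA makes the same common-variance assumption, and changing the t-test does not repair it.

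This is a change of wording only. It needs no new data, no change in sample size and no prior knowledge of the SD ratio. The cost is about 0.1 point of power if the SDs turn out to be equal.
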